### Measurement instruments

The primary outcome will be measured by means of the questionnaire for the assessment of empowerment in patients with affective and schizophrenic disorders (EPAS). The EPAS measures empowerment as the patient’s perceived opportunity to control their own living circumstances on five dimensions: “daily living”, “social relationships and sexuality”, “psychiatric treatment”, “hope and self efficacy” and “self esteem”. Additional subscales are available for patients who are employed and for parents of minor children. The EPAS core module has 33 items and a Cronbachs Alpha of .94 was obtained for the total scale [14].

The secondary outcome measures include 1) reduction in psychosocial and clinical impairment using HoNos [Health of the Nation outcome scale] [15-18], 2) improvement of subjective quality of life using WHO-QoL-BREF [World Health Organisation Quality of Life-short version] [19], 3) reduction of unmet needs for psychiatric and psychosocial services using CAN-EU [Camberwell Assessment of Need-European Version] [20,21], 4) increase in satisfaction with psychiatric treatment using ZuF8 [questionnaire to treatment satisfaction] [22,23], 5) reduction of utilisation of stationary and simultaneous increase in utilisation of ambulatory medical and psychosocial services using CSSRI [Client Socio-Demographic and Service Receipt Inventory] [24], 6) reduction of direct and indirect healthcare costs using CSSRI [24], 7) reduction of costs of recovering a “healthy” year of life (QALY) using EQ-5D [Euro Quality of Life – 5 dimensions] [25].

An additional study-specific questionnaire will be used at visit 2, 3 and 4 to gain ancillary information as regards the importance of and the satisfaction with local community mental health services from the patients’ perspective.

There is the following set of outcome measures for relatives and informal carers: 1) Change in perception of burden related to support of patient suffering serious mental illness using IEQ [Involvement Evaluation Questionnaires] [26], 2) change in subjective quality of life using WHO-QoL-BREF [19] and 3) change in satisfaction with psychiatric treatment using ZuF8 [22,23].

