### Sample Size calculation

The sample size calculation is performed for the change in the empowerment total score over 18 months. An effect size of f = 0.2 was assumed to be clinically relevant for the within-between interaction of group*time in repeated-measurements ANOVA with two groups and four time-points of measurement.

Based on this effect size, a power of 0.90, and an alpha level of 0.05, a total sample size of n = 350 is needed. Sample size was further estimated based on a drop-out rate of 30 %, according to experience from the ELAN-study [27,28]. Based on this assumption, a total of 500 patients will be recruited for visit 1. The sample size was calculated using G-Power.

All participating patients will be asked to nominate a relative/informal carer who has regular contact with the patient and who supports the patient with regard to disease-related burden. It is expected that relatives/informal carers of about 50 % of patients will participate in the study. Thus, the sample size for persons of reference will be equal to n = 250. Using a repeated-measurements design with four time-points of measurements this sample size will concede the demonstration of an effect with effect-size f = 0.2 and a significance level of alpha = 0.05 with a power greater than 0.75.

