#### *Statistical analysis*

The primary outcome is the change in empowerment total score of EPAS over 18 months. Normal distribution is assumed. This will be checked, and if found to be lacking than appropriate solution strategies will be applied. Data analysis for the primary outcome will be performed using analysis of variance with repeated measurements with a time effect, a group effect and an interaction effect between time and study group.

In addition, secondary analysis for the primary outcome will include a per-protocol (PP) approach. The PP population will exclude all subjects in the ITT population who meet any of the following criteria:

– change of study group during study process

– non-compliance or infrequent use of integrated care by volunteers in the IC group

– more than four weeks between registration to integrated care and visit 1 for patients in the IC group

– visit 2, visit 3 and visit 4 were outside initially planned time periods (more than +/− 1 month to intended time points: 6 months, 12 months or 18 months after visit 1)

This additional analysis assesses the maximal intervention efficacy in ideal conditions based on comparable outcome measurements.

For secondary endpoints mixed-effect regression models will be used. The random effect of time as well as the interaction effect of time and study group will be adjusted for propensity scores [28].

Within the frame of health economic evaluation based on the net benefit approach, multivariate regression models for the cost-utility relation as dependent variable will be calculated adjusted for the propensity scores. The cost-utility relation is defined as the ratio of direct and indirect costs and the change in QALYs [31-34]. Change in QALYs will be calculated on the basis of EQ-5D questionnaire. All costs will be calculated from a societal point of view, for that reason total costs of care were considered and not just out-of-pocket payments. Furthermore, production losses due to time off work for those in employment will be included in the analyses.

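### The economic regression names net benefit but uses a patient-level cost/QALY-change ratio as its outcome, so the group coefficient cannot be read as value for money

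*Protocol article*

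**What the plan says.** The health economic paragraph of the protocol article (Planned analysis, Statistical analysis) makes three linked statements.

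- The framework: "Within the frame of health economic evaluation based on the net benefit approach".
- The model: "multivariate regression models for the cost-utility relation as dependent variable will be calculated adjusted for the propensity scores".
- The outcome of that model: "The cost-utility relation is defined as the ratio of direct and indirect costs and the change in QALYs".

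On the denominator it adds: "Change in QALYs will be calculated on the basis of EQ-5D questionnaire". Under Measurement instruments, the seventh secondary outcome is again a cost per QALY: "reduction of costs of recovering a “healthy” year of life (QALY) using EQ-5D".

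No willingness-to-pay value (λ) and no linear combination of cost and QALYs appears anywhere in the article. No other section changes the definition.

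**The concern.** Net benefit is a linear quantity, λ × QALYs − cost. It was devised so that analysts need not model a cost-effectiveness ratio. The article names that approach and then defines the regression outcome as the ratio, so the two statements cannot both be followed.

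The article does not use the word individual. But a dependent variable in a regression adjusted for patient propensity scores must take one value per patient, and a group-level incremental ratio cannot fill that role.

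A patient-level ratio has three faults:

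- its meaning reverses when QALY change is negative;
- it is undefined at zero change and dominated by patients close to zero;
- its average is a different quantity from incremental cost per incremental QALY.

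Cost-effectiveness is one of the two things the study sets out to assess (Abstract; end of Background), and the Conclusion addresses the results to funders. Followed as written, the analysis would leave that aim without an interpretable answer.

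**Working it through.** The article states no figure for the economic analysis, so there is nothing to reproduce on this point. Steps 1 to 3 need no assumption about the trial; their patient values only illustrate. Steps 4 to 6 rest on assumed inputs.

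**1. Sign.** Ratio = cost / QALY change; net benefit = λ × QALY change − cost, with λ = 30,000 EUR for illustration.

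| Patient | Cost (EUR) | QALY change | Ratio | Net benefit |
|---|---|---|---|---|
| A | 15,000 | +0.1 | +150,000 | 3,000 − 15,000 = −12,000 |
| B | 15,000 | −0.1 | −150,000 | −3,000 − 15,000 = −18,000 |
| C | 30,000 | −0.1 | −300,000 | −3,000 − 30,000 = −33,000 |

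If a lower cost per QALY is better, the ratio ranks C best and A worst. Net benefit ranks them A, B, C.

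**2. Near zero.** 15,000 / 0.01 = 1.5 million EUR per QALY; at zero change there is no value.

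**3. Wrong average.** Take two patients costing 15,000 each, with +0.1 and +0.3 QALY. The mean of the ratios is (150,000 + 50,000)/2 = 100,000. The ratio of the means is 15,000/0.2 = 75,000.

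**4. No stable mean.** Assume lognormal costs (mean 15,000, coefficient of variation 1) and QALY change distributed N(0.1, 0.2²). The interquartile range of the sample mean ratio was about −25,000 to 119,000 at n = 175 and −44,000 to 123,000 at n = 175,000. It does not shrink as n grows, because the denominator has positive density at zero.

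**5. Effect on the comparison.** I took 175 per group, half of the 350 analysable patients in Sample Size calculation. Assumed: mean QALY change 0.08 (IC) and 0.02 (CAU), SD 0.2; equal lognormal costs, mean 15,000; coefficient of variation 0.8 to 1.2. IC is therefore truly better value. Each setting used 4,000 simulated trials.

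- Negative ratios: Φ(−0.08/0.2) = 0.345 in IC and Φ(−0.02/0.2) = 0.460 in CAU, average 0.40.
- IC − CAU difference in mean ratio: 95% range about −2.1 to +2.3 million EUR per QALY at coefficient of variation 1. It was positive, that is against IC, in 53 to 55% of trials and nominally significant in about 2%.
- Net monetary benefit, λ = 50,000, coefficient of variation 1: true difference 50,000 × 0.06 = 3,000. Patient SD = √(10,000² + 15,000²) = 18,028. SE = 18,028 × √(2/175) = 1,927. Probability of the right sign = Φ(3,000/1,927) = 0.94. Over coefficients of variation 0.8 to 1.2 it is 0.96 to 0.91.
- The same at λ = 30,000: true difference 1,800, SE 1,727, Φ(1.04) = 0.85; range 0.90 to 0.81.

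A second scenario made IC 20% cheaper and 0.05 QALY better, with λ = 30,000 and 3,000 trials per setting. The ratio difference was positive in 46 to 53% of trials. Net benefit had the right sign in 99.8 to 100%.

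**6. Discrete EQ-5D values.** Rounding QALY change to 0.01 and dropping exact zeros (about 2% of patients) removes the most extreme values. At coefficient of variation 1 the 95% range narrows to about −90,000 to +133,000. Over coefficients of variation 0.8 to 1.2 the difference then points against IC in 65 to 67% of trials.

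**The case against.** The strongest reply is that the named method is net benefit, supported by four references not available here, and that the ratio sentence is a loose description of the cost-utility measure. The investigators may have meant a proper net benefit regression. That is possible, and it lowers certainty about what would actually be run. It does not rescue the text, which ties the ratio explicitly to the dependent variable.

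A second reply is that the article promises a detailed statistical plan before analysis. That properly covers the choice of λ, how QALYs are computed, interval methods and acceptability curves, and none of these is counted as missing here. It does not cover a definition the article already states. A plan that follows the definition inherits the fault, and one that departs from it contradicts the published protocol.

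Three points on scale stand:

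- The ratio contrast is rarely significant, so the likely outcome is an uninformative comparison rather than a confident wrong one. With continuous values, 53 to 55% against IC is close to a coin flip.
- The contrast with net benefit depends on the assumed cost spread and λ, hence the ranges above.
- The empowerment primary outcome and the separate cost and service-use outcomes are unaffected.

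**Conclusion.** The concern holds: the dependent variable is wrong as written and contradicts the approach the article names. The sign reversal, the undefined value at zero and the mismatch with the incremental ratio follow from the definition alone.

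The numerical size depends on assumed costs, QALY changes and λ. Under each scenario tried, the direction of the ratio contrast carried little or no information about which programme is better value, while net benefit on the same data usually or almost always had the right sign. The damage is confined to the cost-effectiveness analysis, but that is a stated aim, so the definition must be corrected before the data are analysed.

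**What to change.** Replace the definition of the dependent variable. For each patient, net monetary benefit = λ × QALYs over 18 months − total direct and indirect cost, with QALYs taken as the area under the EQ-5D utility curve. Regress it on study group, propensity score and baseline utility over a stated range of λ.

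Report a cost-utility ratio only at group level, as the adjusted mean cost difference divided by the adjusted mean QALY difference. Align the cost-per-QALY outcome in Measurement instruments with this. Bootstrap intervals and an acceptability curve are sensible additions that the statistical plan can hold.

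If net benefit regression was intended all along, the same edit makes the text say so. The cost is about two sentences. The CSSRI and EQ-5D data are already part of the planned assessments, and sample size and visit schedule do not change.

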## Methods/design

### Study design

Although the randomised clinical trial is considered the gold standard for examining the efficacy of mental health care interventions, legal and organisational aspects prevent this design being applied in the current study: The implementation of integrated care programmes took place on the legal basis of the German social code which authorises the health insurances to define the criteria for the eligibility of patients to enrol in integrated care programmes. In addition, the social code gives patients the right to be informed by sickness funds about the opportunity to enrol in an integrated care programme. If a patient fulfils the eligibility criteria, he or she will be informed by the health insurance and asked for the permission to transmit his or her contact data to the local integrated care provider. After the patient gives his or her permission to the sickness fund the local service provider contacts the patient and invites him or her to attend an informative meeting. On the basis of this interview the service provider decides if the patient will be offered enrolment or not. Finally, the patient decides whether to enrol or not.

Therefore, we decided to design this study as a prospective observational controlled trial comparing patients with severe mental disorders enrolled in an NWpG integrated care programme with patients who received standard care in five federal states (Schleswig-Holstein, Northrhine-Westfalia, Berlin, Saxony and Bavaria) covering a broad range of catchment areas with different levels of urbanization, with different local mental health service systems and with different providers of ACT services. Trial duration is 18 months. Data will be collected at baseline and there will be three follow-ups after 6, 12 and 18 months.

Due to preference-based allocation blinding of patients is not feasible. Furthermore, it is not possible to blind the research associates because they would be unblinded at the latest documenting integrated care service use in the Client Socio-Demographic and Service Receipt Inventory (CSSRI).

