#### *Measures for bias control*

Adjustment based on the propensity score method will be used to control the selection bias [29]. The estimation of propensity scores will be made on the basis of logistic regression models including independent variables such as medical history, patient’s clinical condition, socio-demographic characteristics and current living conditions [28].

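### The economic analysis uses an undefined change in QALYs and does not commit to adjusting for visit-1 EQ-5D or prior costs, so any utility gap the propensity score leaves unbalanced biases the QALY component

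*Protocol article*

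**What the plan says.** The health economic paragraph under Statistical analysis announces a net-benefit approach and continues: "multivariate regression models for the cost-utility relation as dependent variable will be calculated adjusted for the propensity scores". The outcome is then specified: "The cost-utility relation is defined as the ratio of direct and indirect costs and the change in QALYs". On the effect side it adds: "Change in QALYs will be calculated on the basis of EQ-5D questionnaire". No reference point for the change is given, and no adjuster other than the propensity score is named.

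Measures for bias control describes the score as a logistic model "including independent variables such as medical history, patient’s clinical condition, socio-demographic characteristics and current living conditions". The list is illustrative. It includes clinical condition, but it names neither EQ-5D nor earlier costs.

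On timing, Study design states: "Data will be collected at baseline and there will be three follow-ups after 6, 12 and 18 months". Measurement instruments does not tie EQ-5D or CSSRI to particular visits. The one instrument it restricts is a different one: "An additional study-specific questionnaire will be used at visit 2, 3 and 4". Collection of EQ-5D and CSSRI at visit 1 is therefore a reasonable inference, not an explicit statement.

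**The concern.** A QALY is utility accumulated over time. With EQ-5D at four visits, the patient-level quantity over 18 months is the area under four utility values, and a change in that quantity has no single meaning. It could be the area itself, the area minus baseline utility carried forward for 1.5 years, or simply last minus first utility. These readings treat a baseline difference between the groups differently.

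Such a difference is plausible on the article's own account. Under Study design, the provider decides whether to offer enrolment and the patient decides whether to accept. Under Intervention, that provider carries the budget risk for psychiatric inpatient and outpatient clinic costs. Under Trial recruitment process, controls come partly from other settings and partly from patients who declined integrated care. Selection could therefore follow severity and expected cost, which are the two baseline quantities that the plan does not commit to adjusting for.

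Cost-effectiveness is one of the two questions in the study's stated focus, and the Conclusion addresses the results to purchasers. A spurious QALY difference would feed directly into that answer. This is separate from the choice of a cost-to-QALY ratio as outcome: it would remain if net benefit were regressed instead.

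**Working it through.** **The plan's own figure.** There is none to reproduce. The article gives no EQ-5D mean, standard deviation, correlation or expected baseline gap, and its sample size concerns the EPAS score. The sizes below rest on assumptions.

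**Inputs.**
- Visits at 0, 6, 12 and 18 months (Study design). Trapezoid weights are 0.25, 0.5, 0.5 and 0.25 years, which sum to 1.5.
- g: the part of the visit-1 utility gap (integrated care minus usual care) that the propensity score leaves unbalanced. Assumed 0.05, with 0.03 as a smaller case.
- b: slope of follow-up utility on visit-1 utility. Assumed 0.5, range 0.4 to 0.7.
- No true treatment effect, so the expected gap at each follow-up is b·g.

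**Formulas.**
- Raw area: 0.25g + (0.5 + 0.5 + 0.25)·b·g = g(0.25 + 1.25b).
- Area minus 1.5 × baseline: g(0.25 + 1.25b) − 1.5g = −1.25g(1 − b).

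For any b strictly between 0 and 1 the two have opposite signs. At b = 1 the second is zero.

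| g | b | Raw area | Area minus 1.5 × baseline |
|---|---|---|---|
| 0.05 | 0.4 | +0.038 | −0.038 |
| 0.05 | 0.5 | +0.044 | −0.031 |
| 0.05 | 0.7 | +0.056 | −0.019 |
| 0.03 | 0.5 | +0.026 | −0.019 |

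For g = 0.05 and b = 0.5: 0.05 × (0.25 + 0.625) = 0.04375, and −1.25 × 0.05 × 0.5 = −0.03125. If integrated care starts lower instead of higher, all signs flip.

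**How much of the gap the score removes.** This was simulated with 500 patients, 600 repetitions, utility SD 0.25 (assumed), slope 0.5 and no treatment effect. Integrated care starts 0.05 lower, so the signs are the reverse of those in the table above.

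| Adjustment | Raw area | Area minus 1.5 × baseline |
|---|---|---|
| None | −0.045 | +0.032 |
| Score without any health variable | −0.044 | +0.032 |
| Score with a clinical variable correlated 0.5 with utility | −0.033 | +0.024 |
| Score that also contains visit-1 EQ-5D | 0.000 | 0.000 |
| Clinical score plus visit-1 EQ-5D as covariate | 0.000 | 0.000 |

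The clinical score leaves about three quarters of the bias (0.033/0.045 and 0.024/0.032). Entering visit-1 EQ-5D, in either place, removes it.

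**Precision.** Between the clinical score alone and the clinical score plus EQ-5D as covariate, the standard deviation of the estimate falls from 0.022 to 0.015 for the raw area and from 0.020 to 0.015 for the change version.

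**Why the covariate also settles the definition.** The raw area and the area minus 1.5 × baseline differ only by a multiple of visit-1 utility. Once that utility is a covariate, both give the same group estimate.

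**The case against.** **Left to a later plan.** Planned analysis promises a detailed statistical plan before the data are analysed, and QALY construction and covariate lists often sit there. That plan is not shown and may settle the matter. What stands is that the article itself fixes the effect as a change and names one adjuster, and that this wording permits analyses whose biases have opposite signs.

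**The propensity score may already cover it.** A reader might infer that every baseline utility gap enters the QALY result, that the regression excludes all covariates except the score, or that the score omits baseline health. The documents support none of these. The covariate list is open and includes clinical condition, under which EQ-5D could fall, and the article calls the regression multivariate without excluding further terms. Only the unbalanced part of the gap matters.

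**The change score may be the right one.** If the two groups would have kept a constant gap g without treatment, subtracting baseline is unbiased. Covariate adjustment would then be off by 1.5g − g(0.25 + 1.25b) = 1.25g(1 − b), or +0.031 for g = 0.05 and b = 0.5. This is Lord's paradox, and the data cannot exclude it. It carries limited weight here because the plan already relies on comparability given measured baseline factors through the propensity score. It does justify a sensitivity analysis.

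**Visit 1 is not a clean baseline.** Data collection/management process places it within the first month of registration for integrated care, so early programme contact may already show. This is a real but small limit, and a change score shares it.

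**Conclusion.** The point holds in a limited form. The change in QALYs is undefined, and nothing in the article commits the analysis to visit-1 EQ-5D or prior costs, either in the propensity model or in the economic regression. A utility gap that the score leaves unbalanced biases the QALY component, in a direction that depends on how the change is taken.

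The figures of +0.044 and −0.031 QALY are a worst case in one respect: they assume that the score removes none of a 0.05 gap, with slope 0.5 and follow-up utility regressing along that slope. Partial balance shrinks them, and visit-1 EQ-5D in the score brings them to about zero. Gap, slope and SD are assumptions, and the direction of any gap is unknown. The figures describe the QALY component and do not carry over additively to the cost-to-QALY ratio that the article names as dependent variable. No size can be given for a baseline cost gap. The wording should be settled before the analysis.

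**What to change.** In the analysis plan still to be written:

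- Replace the change in QALYs by 18-month QALYs, computed per patient as the trapezoid area under EQ-5D utility at 0, 6, 12 and 18 months.
- Enter visit-1 EQ-5D and visit-1 CSSRI costs (prior period) as covariates next to the propensity score in the QALY, cost and net-benefit regressions.
- State explicitly whether these two variables also enter the propensity model.
- Keep a change-from-baseline analysis as a sensitivity check, since it rests on the alternative assumption of a constant gap.
- Confirm that EQ-5D and CSSRI are taken at visit 1.

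If visit-1 collection is confirmed, this changes wording only and needs no new data. The downside is small: for integrated-care patients seen some weeks after enrolment, the baseline covariates could absorb a little early effect. The adjustment also assumes comparability given measured baseline values, as the propensity score already does.
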